### 2.8. Objectives

The primary objective is to develop an HRQoL measurement strategy for sarcoma patients, indicating which issues can be included for all sarcoma patients (sarcoma-generic) and which issues should be evaluated in certain subgroups (e.g., based on treatment or sarcoma location) only. This is the first step towards the implementation of sarcoma specific PROs in future clinical trials. Secondary endpoints are: (1)to develop an exhaustive list of all HRQoL issues relevant to sarcoma patients (irrespective of their sarcoma subtype, treatment, time since diagnosis and age, and including generic/specific issues), (2) to determine the proportion of patients in each subgroup (according to tumor localization, type of sarcoma, disease stage and treatment) rating each item and the items from the EORTC QLQ C30 as relevant (i.e., rating 2–4 on Likert scale indicates relevance), (3) to determine the proportion of respondents with head neck or uterine localization rating each site-specific item of the H&N43 or EN24 questionnaire as relevant (i.e., rating 2–4 on Likert scale indicates relevance), (4) to determine the proportion of subgroups rating each item as relevant (i.e., half subgroups rating an item as relevant indicates a sarcoma-generic issue), and (5) to determine subgroup-specific (according to localization, type of treatment, subtype and disease stage) issues using a comparative approach (issues cited at least 1.5 times more indicates subgroup-specificity).

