### 2.9. Sample Size Calculation

Part A: No formal sample size calculation can be made for the interviews. Data collection continues until saturation is reached, which is usually after 12 patients in phenomenological research [49]. Saturation occurs when adding more participants to the study (or, in this case, subgroup) does not result in additional perspectives or information. A stratification matrix (Table 1) will be used that ensures that at least 12 patients per location and 10 per treatment will be interviewed, considering the incidence of sarcoma location and treatment. In total, 154 patients will be recruited. Although some locations will be overrepresented in this sample compared to the population-based incidence numbers, this proportion was chosen to make sure that enough patients are enrolled per group to be able to conduct subgroup analyses.

Part B: Although the EORTC guidelines for development state that no more than 10 patients should be included in this part, the heterogeneity of the sarcoma population requires greater numbers for adequate subanalyses. Again, at least 10 patients per location and 10 per treatment will be recruited (Table 1), leading to a total of 475 patients.

Healthcare professionals: According to the EORTC module development guidelines, at least 5 HCPs should be included; therefore, 5 HCPs will be interviewed for each location (i.e., 6 in total), which means 30 HCPs in total. This applies to both parts A and B.

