### 2.10. Statistical Analysis

We will perform thematic analysis of the qualitative data. Transcripts of the patient and HCP interviews will be examined by two coders in detail in order to identify basic patterns and recurrent themes using line-by-line coding to examine, compare and begin to develop conceptual categories. Categories will be developed inductively using the constant comparison method. Comparing each item with the rest of the data to create analytical categories, and then grouping categories together will make it possible to identify key themes [50]. The consolidated criteria for reporting qualitative research (COREQ) will be followed to ensure the accuracy of this qualitative study [51].

Data from patient and HCP interviews and questionnaires will be analyzed according to the EORTC module development guidelines [36], using basic quantitative analyses, including descriptive statistics (e.g., missing data, means and standard deviations, floor and ceiling effects), prevalence (number of patients who experienced each complaint, i.e., who scored 2, 3 or 4, divided by the total number of patients who completed that item, multiplied by 100), priority ratings (number of patients and professionals who have given priority ratings to each item) and range of responses for each item.

In order to facilitate transparent decision-making concerning the best approach to take in developing a sarcoma measurement strategy, the existing decision criteria will be followed: (1) an inclusive approach will be taken with regard to relevant items; (2) inclusion of an issue will be considered when more than 30% of patients (in total or per subgroup) mention the issue as missing; (3) issues that have a low (e.g., mean <1.5) mean score for relevance or importance will be considered for exclusion.

To distinguish “sarcoma generic” from “subgroup-specific issues”, issues that are more or less frequent in specific subgroups will be evaluated. An issue will be coded as endorsed by a respondent if it was scored 2 (“a little relevant”) or higher on the 4-point response scale. An issue needs to be endorsed by at least 30% of the patients in a subgroup to be included as an issue in that subgroup. If an issue is endorsed by patients from 3 out of 6 tumor locations and 2 out of 4 treatment groups, it will be considered to be a generic sarcoma issue; otherwise, it can be considered a sarcoma subgroup-specific issue.

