Additional analyses will be performed per subgroup for location, treatment(s) received (surgery; chemotherapy/targeted therapy; radiotherapy; no treatment), type of sarcoma (soft tissue vs. bone sarcoma), and disease stage (localized vs. metastatic). An issue needs to be endorsed by at least 30% of the patients in a subgroup, and the mean score needs to be 1.5 or higher to be included as an issue in a subgroup. Then the prevalence of each issue between the aforementioned subgroups (according to location, type of treatment, subtype and disease stage and combinations of these factors) will be compared to decide whether an issue is subgroup-specific. Issues that are cited by at least 1.5 times as many respondents in group A compared to group B (a ratio of 3:2) may be considered as subgroup-specific.

For head and neck, and uterine sarcoma patients, the scores on the H&N43 and EN24 will be analyzed. We will assess the prevalence (percentage of the subjects who score higher than 2 is >30% and a mean score of 1.5 or higher) of each site-specific item. When at least 80% of the items are prevalent, using the site-specific module for those sarcoma locations will be recommended.

All the collected information will help to advise researchers as to which factors need to be taken into account when creating an item list for a specific study focusing on subgroups of sarcoma patients.

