**Total**							
Per location	210	40	65	40	80	40	475
Per treatment							
SU only:							99
SU + RT:							96
SU + RT + ST:							40
Surgery total:							235
RT total:							136
ST only:							172
ST total:							212
Local:							38
Per subtype							
Bone:							175
Soft tissue:							300

^a^ Covered by axial group; SU = surgery; ST = systemic therapy (e.g., chemotherapy, tyrosine kinase inhibitors, immunotherapy); RT = radiotherapy; BSC = best supportive care; local treatment = SU and/or RT in metastatic setting.

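### The 1.5 cut-off for subgroup-specific issues is worded as a ratio of numbers of respondents although prevalence is announced as the basis, and Part B group sizes alone would meet it in most location pairs and for soft tissue versus bone

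*Protocol article*

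**What the plan says.** Three parts of section 2.10 and one of section 2.8 bear on the rule.

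- **Definition of prevalence (2.10).** It is the number of patients scoring 2, 3 or 4, "divided by the total number of patients who completed that item, multiplied by 100". It is a percentage with its own denominator.
- **Entry condition (2.10, additional analyses).** "An issue needs to be endorsed by at least 30% of the patients in a subgroup, and the mean score needs to be 1.5 or" more, for the issue to count in that subgroup.
- **Comparison and cut-off (2.10, additional analyses).** The basis is announced first: "Then the prevalence of each issue between the aforementioned subgroups" is to be compared. The next sentence gives the threshold: "Issues that are cited by at least 1.5 times as many respondents in group A compared to group B (a ratio of 3:2"). Such issues may then be treated as subgroup-specific.
- **Secondary endpoint 5 (2.8).** The same threshold appears as "issues cited at least 1.5 times more indicates subgroup-specificity".

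The threshold is thus written twice, and neither statement mentions prevalence, proportion or a denominator.

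Part B has 475 patients (2.9). Table 1 divides them by location as "Per location 210 40 65 40 80 40 475" and by subtype as 175 bone and 300 soft tissue.

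**The concern.** The sentence that decides the label does not use the quantity announced just before it. Comparing prevalences asks whether an issue is more common in group A. Comparing numbers of respondents mixes that question with how many patients each group was allotted. The quotas in Table 1 are unequal on purpose, so the two readings can give different labels for the same issue, and sometimes opposite ones.

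The rule is secondary endpoint 5, and it informs the primary objective of separating issues for all sarcoma patients from issues for certain subgroups only. An analyst who follows the threshold sentence to the letter would partly reproduce the recruitment quotas.

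**Working it through.** **Inputs.** Part B group sizes come from Table 1. The 30% entry condition and the definition of prevalence come from section 2.10. The article gives no expected prevalences, so the values below are assumed.

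**1. Reproduce the group sizes.** Summing the Phase 1b cells by column:

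- extremities 20+20+20+10+40+20+30+10+30+10 = 210
- axial 4+8+8+4+16 = 40
- head and neck 5+4+4+12+4+16+16+4 = 65
- thoracic 12+8+16+4 = 40
- retroperitoneal/intra-abdominal 24+16+32+8 = 80
- pelvic organs 20+16+4 = 40

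The total is 475, as stated. The row sums give bone 175, soft tissue 300, localized 235 and metastatic/relapse 240, all as stated.

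**2. Evenly spread issue, count reading.** With the same prevalence p in both groups, the ratio of expected counts is (n_A × p)/(n_B × p) = n_A/n_B, so p cancels.

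| Larger v smaller group | n_A/n_B | Reaches 1.5? |
|---|---|---|
| Extremities v axial, thoracic, pelvic (3 pairs) | 210/40 = 5.25 | yes |
| Extremities v head and neck | 210/65 = 3.23 | yes |
| Extremities v retroperitoneal | 210/80 = 2.63 | yes |
| Retroperitoneal v axial, thoracic, pelvic (3 pairs) | 80/40 = 2.00 | yes |
| Head and neck v axial, thoracic, pelvic (3 pairs) | 65/40 = 1.63 | yes |
| Retroperitoneal v head and neck | 80/65 = 1.23 | no |
| Among the three groups of 40 (3 pairs) | 1.00 | no |
| Soft tissue v bone | 300/175 = 1.71 | yes |
| Metastatic/relapse v localized | 240/235 = 1.02 | no |

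That is 3+1+1+3+3 = 11 of 15 location pairs, plus the subtype pair.

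For treatment, Table 1 totals of surgery 235, systemic 212, radiotherapy 136 and best supportive care 30 give 5 of 6 pairs at or above 1.5; the exception is surgery v systemic, 235/212 = 1.11. This count is only indicative. The totals overlap, and best supportive care is taken as the no-treatment group.

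**3. Chance of a flag for the larger group.** Two independent binomials with the same p, exact calculation, before the entry condition:

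| Pair | p | Count reading | Prevalence ratio |
|---|---|---|---|
| Soft tissue v bone | 0.4 to 0.6 | 88% to 96% | under 0.1% |
| Extremities v axial | 0.4 to 0.6 | about 100% | 4.8% to 0.7% |
| Retroperitoneal v axial | 0.4 to 0.6 | 90% to 97% | 6.5% to 1.2% |
| Head and neck v axial | 0.4 to 0.6 | 64% to 70% | 6.3% to 1.2% |

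The prevalence ratio is not free of chance flags in groups of 40, but group size no longer drives it.

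**4. Flags for the smaller group.** On counts, the smaller group must have 1.5 × n_A/n_B times the prevalence of the larger. That is 1.5 × 300/175 = 2.6 for bone over soft tissue, and 1.5 × 210/40 = 7.9 for axial over extremities.

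The entry condition sharpens this. An issue that qualifies in extremities has at least 0.30 × 210 = 63 endorsers. To be axial-specific on counts it would need 1.5 × 63 = 94.5 axial endorsers, and there are only 40 axial patients. It can never be flagged.

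**5. A reversal that usually clears the entry condition.** Take an issue endorsed by 70% of axial and 35% of extremity patients.

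- Prevalence ratio: 0.70/0.35 = 2.0 in favour of axial.
- Expected counts: 0.70 × 40 = 28 v 0.35 × 210 = 73.5, a ratio of 2.6 in favour of extremities.

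With the 30% condition applied, the count reading labels it extremity-specific in about 95% of draws. The prevalence ratio labels it axial-specific in 98%. The mean-score part of the condition is taken as met.

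**The case against.** The best defence is that the threshold sentence should be read with the one before it. Prevalence is to be compared, prevalence is defined as a percentage, the neighbouring 30% rules are percentages, and secondary endpoints 2 to 4 speak of proportions. On that view the 1.5 is simply the cut-off for a prevalence comparison. This is a fair account of the likely intent, and nothing shows that the sponsor plans to divide raw counts. It does not repair the sentence, which names people and not proportions.

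Three further limits stand.

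- **Weight of the rule.** It sits among the additional analyses, and section 2.10 only allows the label; section 2.8 is firmer. The main rule, endorsement in 3 of 6 locations and 2 of 4 treatment groups, would be expected to class an evenly spread issue at 40–60% as generic.
- **Size of the multiplier.** A reader might infer from section 2.8 that 1.5 times more means 2.5 times as many. The 3:2 ratio in section 2.10 excludes that. Nor are there three rival rules: there are two statements of one threshold and a conflicting announced basis.
- **Reversal at low endorsement.** A reader might expect an issue at 60% axial and 20% extremity to be relabelled extremity-specific. The entry condition blocks this: 63 of 210 endorsers are needed, 42 are expected, and the chance of reaching 63 is 0.04%. Reversal needs prevalence in the larger group to be around 30% or more, as in the 70% v 35% case.

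**Conclusion.** The point holds as a defect in the wording of a decision rule. The stated cut-off conflicts with its announced basis. Read literally, the planned Part B sizes alone would meet it in 11 of 15 location pairs and for soft tissue versus bone. It does no harm where groups are of similar size, such as localized versus metastatic/relapse.

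The stronger conclusion, that the study will compare counts and so mislabel issues, is not supported: a prevalence ratio is the more likely intention. Nor would the literal reading settle the generic/specific split alone, because the main rule stands beside it.

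The ratios assume recruitment to plan and similar item completion across groups. The probabilities also assume prevalences of 40–60%, or 70% v 35% in the reversal example.

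**What to change.** State the cut-off once, in the same terms, in sections 2.8 and 2.10:

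> An issue may be considered subgroup-specific when its prevalence in group A is at least 1.5 times its prevalence in group B, where prevalence is the number of patients in the group scoring 2–4 divided by the number in that group who completed the item.

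This replaces the reference to numbers of respondents in 2.10 and the looser multiplier in 2.8. It also gives both sections the same permissive force.

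The cost is one sentence in each section. Data collection, sample size and the main generic rule are unchanged.

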### 2.7. Questionnaires

Three existing EORTC quality of life questionnaires will be reviewed by patients and HCPs, for the topic and item relevance. The EORTC QLQ-C30 is provided for all patients, the EORTC QLQ-H&N43 for patients with sarcoma in the head and neck region and the EORTC QLQ-EN24 for patients with uterine sarcoma. Before the start of phase 1b, based on the issues found in phase 1a, it will be evaluated if more location-specific modules (e.g., prostate, breast or colorectal) can be included. All scales and single-item measures range from 0 to 100 after linear transformation. A higher score on functional scales and global QoL means better functioning and HRQoL, whereas a higher score on the symptom scales means more complaints.

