#### 2.7.3. EORTC-QLQ-Endometrial Cancer Module (EORTC QLQ-EN24)

The EORTC QLQ-Endometrial Cancer Module (EORTC QLQ-EN24) was developed for HRQoL measurement in patients with endometrial cancer and consists of 24 items [48]. It has been translated into and linguistically validated in 35 languages. Five symptom scales (lymphedema, urological symptoms, gastrointestinal symptoms, poor body image and sexual/vaginal problems), five single symptoms items (pain in back and pelvis, tingling/numbness, muscular pain, hair loss and taste change) and three single functional items (sexual interest, sexual activity and sexual enjoyment) are measured.

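### If the EN24 cut-off in section 2.10 is applied to completed responses, it misjudges the three functional items when function is largely lost or largely kept

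*Protocol article*

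**What the plan says.** Section 2.10 (Statistical Analysis) states that for head and neck and uterine patients "the scores on the H&N43 and EN24 will be analyzed". An item counts as prevalent under one condition: "We will assess the prevalence (percentage of the subjects who score higher than 2 is >30% and a mean score of 1.5 or higher"). The consequence follows: "When at least 80% of the items are prevalent, using the site-specific module for those sarcoma locations will be recommended". No exception is made for the direction of an item. Elsewhere in the same section, prevalence is described as having experienced a complaint, shown by a raised score.

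Section 2.7.3 says that the EN24 "consists of 24 items". Besides symptom scales and single symptom items, "three single functional items (sexual interest, sexual activity and sexual enjoyment) are measured". Section 2.7 gives the direction of scoring: "A higher score on functional scales and global QoL means better functioning and HRQoL, whereas a higher score on the symptom scales means more complaints". That statement refers to scores after transformation to 0–100.

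The documents describe two different tasks for the patient. In section 2.4.3 (Part B), patients rate the new issue list for relevance but fill in the EN24 itself. Secondary endpoint 3 in section 2.8 concerns the share of patients who rate each EN24 item as relevant, with 2 to 4 counting as relevant. Sections 2.4.2 (Part A) and 2.7 also speak of reviewing the modules for relevance.

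**The concern.** An upward cut-off suits a symptom item: a high score means a problem, and many high scores show that the item matters in this population. For a functional item answered as a self-report, a high score means that function is preserved. A group that has largely lost sexual interest or activity would score low, and the item would be called not prevalent. A group without difficulty would score high, and the item would be called prevalent. In those two situations the rule gives the opposite of what it is meant to detect.

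At stake is the EN24 recommendation for uterine sarcoma, which depends on a count of items that pass. The H&N43 is not affected, because section 2.7.2 lists no functional items for it.

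**Working it through.** **Inputs.** 24 EN24 items, 3 of them functional, so 24 − 3 = 21 others (section 2.7.3). Item rule: more than 30% score above 2, that is 3 or 4, and the mean is at least 1.5. Module rule: at least 80% of items pass (both section 2.10). Assumptions: the score is the completed 1–4 response, and a high response on the three items means better function. The plan gives no calculation of its own to reproduce.

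**Step 1: one functional item.** Let h be the share scoring 3–4. Reverse-coding replaces x by 5 − x, so the share above 2 becomes 1 − h. As written, the 30% condition needs h > 0.30. Reversed, it needs 1 − h > 0.30, that is h < 0.70.

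The mean condition adds nothing. With h > 0.30 the smallest possible mean is 3h + 1(1 − h) = 1 + 2h > 1.6, and the same holds after reversal.

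| Share scoring 3–4 | As written | Reversed |
|---|---|---|
| 30% or less (function largely lost) | not prevalent | prevalent |
| between 30% and 70% | prevalent | prevalent |
| 70% or more (function largely kept) | prevalent | not prevalent |

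Enumerating every response distribution for 40 patients confirms this. The two verdicts differ for shares up to 0.30 and from 0.70 upwards, they agree from 0.325 to 0.675, and the mean condition decides no case. The 40 is illustrative: it is the phase 1b total for pelvic organs in Table 1, and the number with uterine sarcoma is not given.

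**Step 2: the module, function largely lost.** 0.80 × 24 = 19.2, so 20 items must pass and 4 may fail.
- All three functional items fail: up to 21/24 = 87.5% can still pass, but 20 of the other 21 are needed (20/21 = 95.2%).
- All three are reversed and pass: 20 − 3 = 17 of the other 21 are needed (17/21 = 81.0%).
- All three are left out: 0.80 × 21 = 16.8, so 17 of 21 are needed.

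| Other items passing (of 21) | As written, 3 fail | Reversed, 3 pass | 3 left out |
|---|---|---|---|
| 16 | no | no | no |
| 17, 18 or 19 | no | recommend | recommend |
| 20 or 21 | recommend | recommend | recommend |

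If only one or two functional items fail, 18 or 19 of the others are needed (17 + 1, 17 + 2), so the band is narrower.

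**Step 3: function largely kept.** With 70% or more scoring 3–4 on all three items, they pass as written and 17 others suffice. Reversed, they fail and 20 others are needed. The same band of 17 to 19 changes, now from recommended to not recommended. Leaving the items out still requires 17, so the two remedies can differ here.

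**Step 4: which score is used.** Section 2.4.3 separates rating the issue list from filling in the modules, and section 2.10 analyses module scores with a cut-off above 2. Section 2.8 uses relevance ratings with a cut-off of 2 or more. The two rules are therefore not the same, and neither section refers to the other.

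**The case against.** The strongest objection is that the scores may be relevance ratings. Secondary endpoint 3 defines an analysis of these very items in these very patients as a relevance proportion. Section 2.4.2 has the core questionnaire and any site-specific module scored for relevance in Part A, section 2.7 says the questionnaires are reviewed for relevance, and section 2.11 describes missing items as those not rated for relevance. A patient who has lost sexual interest can rate the item very relevant, and direction then plays no part. This stands, and it makes the point conditional. It does not remove the point, because section 2.4.3 describes completion rather than rating, and section 2.10 works on the module scores.

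The second objection also stands. Section 2.7 gives direction only after the 0–100 transformation, and a linear transformation can keep or reverse direction. The cut-offs of 2 and 1.5 make sense only on raw 1–4 scores. That a raw high response is favourable on these three items is inferred from their names.

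Third, the result is advice to researchers, the plan takes an inclusive approach to relevant items, and single items can be drawn from the Item Library (section 1). Missing the 80% mark would not by itself remove sexual function from the strategy. This limits the consequence but leaves a stated rule that can give the wrong answer.

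Finally, recoding is often left to a fuller document. Here, though, the article itself sets out the decision rule, and does so for every site-specific item.

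**Conclusion.** The point holds conditionally, with moderate confidence. If the section 2.10 cut-off is applied to completed EN24 responses, and if high raw responses on the three functional items are favourable, each item is misjudged when 30% or fewer, or 70% or more, of patients score 3–4. With all three misjudged, the recommendation changes when 17, 18 or 19 of the other 21 items pass, and otherwise does not. Only the EN24 and uterine sarcoma are affected. If the cut-off is applied to relevance ratings, the problem does not arise.

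A reader might infer more, and the documents do not support it:
- That three of the 24 items always count in reverse. Between 30% and 70% the verdict is the same in either direction.
- That growing impairment steadily lowers the chance of a recommendation. The rule is a threshold, and an item's verdict changes only once at least 70% score 1–2 on it.
- That the three items can sink the module alone. They use 3 of the 4 permitted failures.
- That the protocol settles on completed responses. Sections 2.4.3, 2.8 and 2.10 do not agree on this.

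**What to change.** Reconcile sections 2.4.3, 2.8 and 2.10 by stating whether the EN24 cut-off applies to completed responses or to relevance ratings, and align the differing cut-offs (above 2, against 2 or more) at the same time.

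If completed responses are meant, confirm the raw direction of the three functional items and then choose one of two options:
- reverse-code them before applying the 30% condition and the mean; or
- leave them out and apply 80% to the other 21 items, that is 17 or more.

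Because the two options can disagree when function is largely kept, fix the choice before Part B data are analysed.

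The cost is a sentence in section 2.10, matching wording in sections 2.4.3 and 2.8, and at most one recoding step, with no new data. If relevance ratings are meant, no recoding is needed, but section 2.4.3 should then say that Part B patients rate the EN24 items. As written, it describes such ratings only for the issue list.

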#### 2.7.2. EORTC-QLQ-Head and Neck Module (EORTC QLQ-H&N43)

The EORTC QLQ-Head and Neck Module (EORTC QLQ-H&N43) measures HRQoL in patients with head and neck cancer [47]. It has been translated into and linguistically validated in 29 languages. It consists of 43 items, divided into 12 symptom scales (pain in the mouth, swallowing, problems with teeth, dry mouth and sticky saliva, problems with senses, speech, body image, social eating, sexuality, problems with shoulder, skin problems and fear of progression) and 7 single items (problems opening the mouth, coughing, social contact, swelling in the neck, weight loss, problems with wound healing and neurological problems).

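### The rule for recommending the H&N43 or EN24 counts only scores 3 and 4, while the protocol's own definitions of prevalence and relevance count scores 2, 3 and 4

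*Protocol article*

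**What the plan says.** Four statements in the protocol article bear on when a module item counts.

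- Section 2.8, secondary endpoint 3, is the proportion of head and neck or uterine respondents "rating each site-specific item of the H&N43 or EN24 questionnaire as relevant (i.e., rating 2–4 on Likert scale indicates relevance").
- Section 2.10, in the general analysis paragraph, defines prevalence from the number of patients "who scored 2, 3 or 4, divided by the total number of patients who completed that item".
- Section 2.10, on issues: "An issue will be coded as endorsed by a respondent if it was scored 2 (“a little relevant”) or higher on the 4-point response scale". The subgroup rule then adds a mean condition, with 1.5 as the minimum: "An issue needs to be endorsed by at least 30% of the patients in a subgroup, and the mean score needs to be 1.5 or" (the sentence is cut short here).
- Section 2.10, on the two modules, gives the test for a prevalent item as "percentage of the subjects who score higher than 2 is >30% and a mean score of 1.5 or higher".

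The last of these drives a decision: "When at least 80% of the items are prevalent, using the site-specific module for those sarcoma locations will be recommended". On module length, section 2.7.2 says of the H&N43 "It consists of 43 items", and section 2.7.3 describes the EN24 as a module for "endometrial cancer and consists of 24 items".

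**The concern.** Three of the four statements put the cut at 2 or higher. The one that governs the module recommendation puts it above 2, which drops the second response category altogether. The word prevalence is thus used with two meanings within section 2.10, and the module rule disagrees with the endpoint it serves. No sentence says that a stricter cut-off is intended for the modules or gives a reason for one.

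The affected output is the advice on whether the H&N43 should be used in head and neck sarcoma and the EN24 in uterine sarcoma, which forms part of the measurement strategy named as the primary objective. With both cut-offs in the text, an analyst could choose between them after seeing the scores, and so choose the recommendation.

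**Working it through.** The plan states no power or error rate for this rule, so there is no figure of its own to reproduce. The check compares what each cut-off implies.

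**Inputs.** Items: 43 and 24 (sections 2.7.2 and 2.7.3). Patients: Table 1, phase 1b. The head and neck cells add up as 5 + 4 + 4 + 12 + 4 + 16 + 16 + 4 = 65, and the pelvic organ cells as 20 + 16 + 4 = 40. Both match the stated location totals. Uterine patients are an unstated part of the 40, so 40 is an upper bound for the EN24.

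**Items needed.** 0.8 × 43 = 34.4, so 35 items. 0.8 × 24 = 19.2, so 20 items.

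**Does the mean condition do any work?** Let s be the share of patients at or above the cut-off. The lowest possible mean arises when everyone else scores 1 and those s score the lowest qualifying value.

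- Cut-off above 2: minimum mean = 1 × (1 − s) + 3 × s = 1 + 2s. With s > 0.30, the mean exceeds 1.6. The condition of 1.5 or higher is then always met.
- Cut-off 2 or higher: minimum mean = 1 × (1 − s) + 2 × s = 1 + s. With s > 0.30, the mean need only exceed 1.3, so the 1.5 condition can exclude items.

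Enumerating every possible set of counts at n = 65 and n = 40 confirms this. Under the stricter cut-off, no case fails on the mean.

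**Direction of disagreement.** In the same enumeration, 9,408 sets of counts at n = 65 and 2,498 at n = 40 are prevalent under 2 or higher but not under above 2. None go the other way. The stricter wording can only remove items.

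**One item.** Assume 1/2/3/4 scored by 40/35/15/10% of patients. Then 60% score 2 to 4, 25% score 3 or 4, and the mean is 0.40 + 0.70 + 0.45 + 0.40 = 1.95. With n = 65, more than 30% means at least 20 patients (19/65 = 29.2%, 20/65 = 30.8%). The binomial probability of 20 or more is above 0.999 with p = 0.60 and 0.175 with p = 0.25.

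**Whole module.** Assume that all items share one distribution and are independent. The probability that the module is recommended (4,000 simulations per row) is:

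| Assumed 1/2/3/4 (%) | Share 2–4 | Share 3–4 | H&N43, n = 65: 2 or higher / above 2 | EN24, n = 40: 2 or higher / above 2 |
|---|---|---|---|---|
| 55/25/12/8 | 45% | 20% | 1.00 / 0.00 | 0.98 / 0.00 |
| 45/30/15/10 | 55% | 25% | 1.00 / 0.00 | 1.00 / 0.00 |
| 35/30/20/15 | 65% | 35% | 1.00 / 0.50 | 1.00 / 0.09 |

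If 40% score 3 or 4 on every item, the H&N43 is recommended with probability 0.9998 even under the stricter cut-off, so the two wordings then agree for that module.

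**The case against.** The best defence is that the two cut-offs serve different purposes. Endpoint 3 reports the share of patients rating an item as relevant. The module rule works on the scores of completed modules, and a plan may report one proportion and apply a stricter bar before recommending a whole module. This does not remove the conflict. The general definition in section 2.10 is framed in terms of complaints experienced, covers questionnaire data, and still counts 2, 3 and 4. The module rule uses the same term without marking an exception. Nor can the cut-off refer to the 0 to 100 transformed scale of section 2.7, since a mean threshold of 1.5 would make no sense there.

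Parts of the case against do stand:

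- The redundant mean condition suggests a slip but does not prove one. A deliberate stricter bar with a mean condition carried over is possible.
- The score distributions above are assumptions, and some lie where the rules disagree most. The recommendation can change; it need not.
- The output is advisory, covers two tumour sites, and does not enter the classification of issues as generic or subgroup-specific.
- A smaller mismatch remains. The module rule requires more than 30%, while the issue rule requires at least 30%. At n = 40 that is 13 against 12 patients; at n = 65 both need 20.
- If completed scores are used, a high score on the three functional EN24 items is not a complaint, so the text should say which scores feed the rule.

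**Conclusion.** The module rule is wrong as written: its cut-off contradicts secondary endpoint 3 and the definition of prevalence in its own section. The reading best supported is 2 or higher. It agrees with those two statements and with the parallel subgroup rule, which pairs the same 30% and 1.5 thresholds with endorsement at 2 or higher, and it is the only one of the two under which the mean condition has any effect.

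In size, the stricter wording can turn a near-certain recommendation (0.98 to 1.00) into one with probability 0.00 to 0.50 for the distributions tried. These figures rest on assumed, identical and independent item distributions and, for the EN24, on all 40 pelvic patients being uterine cases. The contradiction itself rests on the text alone. Because this is a decision threshold fixed in advance, it must be corrected before the data are analysed.

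**What to change.** In the module paragraph of section 2.10, change the cut-off to a score of 2 or higher, so that it matches endpoint 3 in section 2.8 and the general definition of prevalence. Apply the 80% rule (35 of 43 items, 20 of 24 items) on that definition only. In the same edit, use one form of the 30% inequality for issues and module items, and state whether relevance ratings or completed-module scores feed the rule, including for the functional items of the EN24. If a stricter bar for modules is in fact intended, it should be declared as an exception with its reason, and the mean condition, which then has no effect, should be dropped.

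The cost is a few words, changed before the Part B analysis. Data collection and sample size are unaffected.
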